#### *Randomisation and Allocation Concealment*

Randomisation service will be provided by an independent statistical support service based in the UK. We will stratify randomization based on severity of depressive symptoms at baseline and study centre. Participants will be assigned to groups via random generation of allocation sequence, balanced across allocation group. Each participant will be assigned a unique study patient identification number once they have given informed consent and eligibility has been confirmed. The central trial pharmacist will prepare a 12-week package of treatment bearing the patient's name and ID number and send it to the site pharmacy. Thus, the site pharmacy will not know the treatment allocated to the patient. A study information leaflet will be given

to the participant, explaining that they are in a clinical trial and that in addition to TAU they are taking a placebo or simvastatin. This leaflet will also have the name of the local PI's.

Allocation will be masked from study investigators and co-investigators until participants have completed all follow-ups and the database is cleaned and locked. The trial pharmacist at the central pharmacy will keep the drug codes. There will be detailed protocols regarding maintenance of blindness for raters and governing unblinding procedures in case of emergency for pharmacists. To assess the integrity of blinding procedures, participants and independent raters will be asked to complete a conventional guess form asking whether they believe participants received simvastatin or placebo as a treatment after the final ratings have been completed.

If any participant develops side effects or suffers an emergency requiring drug unblinding, the responsible consultant and care team will be informed of the trial drug, probable side-effects and make a decision of participant continuation in the trial. Participant well being and safety will be crucial at all times and locally and internationally accepted Good Clinical Practice will be observed across the trial's governance procedures

#### *Follow-up*

Participants will continue with the treatment currently provided by their clinical teams. Simvastatin will be started at a dose of 20mg daily. Assessments will be at baseline, weeks 2, 4, 8 and 12.

The clinical team and consultant psychiatrist will continue to oversee routine care for each participant although research assistants will be contactable for the duration of the study to respond to any concerns. Demographic data will be collected by RAs at baseline and will include age, gender, marital status, socio-economic status, highest level of education, smoking status, and concomitant medication.

Participants will be asked to bring all leftover medications to each follow up visit, so that RAs can complete a pill count to monitor compliance. On each visit the research assistant will meet with patient at an agreed location to complete the follow up assessment.

#### *Outcome measures*

The primary outcome measure will be the Montgomery-Asberg Depression Rating Scale (MADRS) [28] total score at week 12. Ratings will be made on the basis of a semi-structured clinical interview at baseline and at every follow-up visit until week 12. The MADRS was chosen as the primary outcome measure as it has been demonstrated to be more precise in estimating changes in depression severity compared to other measures [29, 30]. However the HRSD remains a useful screening tool and the use of different assessment scales at screening and follow-up mitigates the risk of clinician bias whereby raters over-estimate symptom severity at screening stage to increase study recruitment. This can then mask the true treatment effect and may lead to an inflated placebo response.

Other outcomes recorded will include the 24-item Hamilton Rating Scale for Depression (HRSD-24) [25] which includes assessment of atypical depressive symptoms, the Clinical Global Impression (CGI) scale [31], an overall measure of illness severity, the 7-item

Generalized Anxiety Disorder scale (GAD-7) [32], a self-report measure of severity for generalised anxiety disorder and a modified Morisky measurement of medication adherence (MMAS-4) [33]. We will also assess changes in body mass index (BMI) from baseline to week 12. All scales have been validated for use in the Urdu language and have been used in previous studies in Pakistan [24]. Adverse effects will be monitored using a side effect assessment scale based on the product monograph of simvastatin.

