### *Screening*

At the first visit, participants will undergo structured diagnostic interviews using the Structured Clinical Interview for DSM-5 (SCID-5) to confirm a diagnosis of DSM-5 current major depressive episode [23]. This tool has been validated for use in the Urdu language and has been used in previous studies in Pakistan [24]. The 24-item Hamilton Rating Scale for Depression (HRSD-24) will be used to assess severity and a score  $\geq 14$  will be used as the minimum threshold for study entry [25].

All patients must currently be on an antidepressant and must have had a non-response to  $\geq 2$  oral antidepressant treatments in the current episode (including the one they are currently

taking). The  $\geq 2$  antidepressants must have been taken for at least 6 weeks at least at the minimum therapeutic dose according to British National Formulary (BNF) [26] and Maudsley prescribing guidelines [27]. Relapse whilst on an antidepressant will also count as a failed treatment trial. During the twelve weeks of active/placebo treatment patients will be requested to remain on a stable dose of the antidepressant they are taking. Participants will not be permitted to start a psychosocial intervention or psychotherapy during the study period, however those who were already engaged in these treatments at the screening stage will be permitted to continue their treatment.

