#### *Exclusion Criteria*

Primary psychotic disorder or bipolar disorder; history of intolerance to statins or presence of any contraindication to statins; presence of any serious medical condition or neurological problem; presence of autoimmune or inflammatory disorder (e.g. systemic lupus

erythematous, rheumatoid arthritis and inflammatory bowel disease); alcohol or drug dependence; active suicidal ideation; pregnant or breast-feeding. Patients with a serum low density lipoprotein (LDL) level of <80 mg/dL at baseline are also excluded from the study as are patients with abnormal hepatic enzymes (Aspartate transaminase (AST) and Alanine transaminase (ALT)) or abnormal Lactate Dehydrogenase (LDH) or Creatinine Phosphokinase (CPK) values at baseline. Patients already on statin treatment will also be excluded.

The criteria for leaving the study are: (1) at the participant's request; (2) at the discretion of the responsible physician or trial investigator (e.g. an adverse event, poor compliance). Poor compliance is defined as either taking <75% of study medication between assessments points at baseline, week 2, 4, 8 and 12 or missing trial medications all together for  $\geq 7$  days in period (3) pregnancy.

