280 To compare response and remission rates between groups logistic regression will be used in  
281 which patients will be classified as in remission or not according to standard criteria on the  
282 MADRS scale. As there are multiple measures, p values will be adjusted for multiple  
283 comparisons using a correction based on controlling the family-wise error. Outcomes at  
284 timepoints other than 12 week follow-up will be considered exploratory and the main focus  
285 will be effect sizes (standardized regression coefficients).

286

287 To compare frequency of adverse events descriptive summaries will be presented by  
288 treatment group. Differences in the rates of AEs will be assessed by generalized linear mixed  
289 model with Poission or negative binomial distribution will be used given sufficient numbers  
290 of events, where time, treatment group and their interaction are fixed effects with subjects as  
291 random effects. Alternatively, simple count models will be used at each timepoint given the  
292 limited sample size and complexity of GLMM models.

293

294 It is likely there will be some drop-out of participants from the trial. Baseline predictors of  
295 missingness can be identified using logistic regression with the outcome (missing or not).  
296 Mixed effect models fitted through maximum likelihood can use all available information in  
297 the data potentially avoiding removal of dropout subjects from the analysis. Moreover, by  
298 including baseline predictors of missingness in the statistical models, the analysis may

assume the data to be missing at random (MAR). Diagnostic analysis will be conducted through checking residuals for outliers, influential data points and normality. If outliers or influential points are found a sensitivity analysis will be conducted after removing such points to see if the main findings change.

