The exploratory hypothesis that baseline lipid/CRP levels will affect response to simvastatin will be tested by adding the baseline lipid/CRP to a model for the primary outcome at 12 weeks, adjusted for baseline and including a treatment group by baseline lipid/CRP. The lipid/CRP level will be considered moderators if interaction with treatment group is significant (at significance level of 0.05, using bootstrapping for inference and construction of confidence intervals). If this is the case, exploratory plots that look at the group effect at different levels of the moderators will be used to study the nature of the moderation.

In order to test the hypothesis that changes in peripheral levels of lipids/CRP will be a mediator in the path between treatment and change in MADRS scores, an initial descriptive analysis will be conducted to look at the bivariate association between treatment group and change in lipid/CRP levels, and between change in lipid/CRP (at 4 and 12 weeks) and change in MADRS scores. A mediation model will then be fitted to the data that joint models the effects of treatment on the change in lipid/CRP at 4 weeks and MADRS at 12 weeks. The mediation effect is tested by the proportion of the total effect from treatment group to change in MADRS that goes through change in lipid/CRP. This model will be fitted in Lavaan in R or Mplus 7.11[35] and the indirect effect estimated through bootstrap resampling. Given the sample size, note the effect sizes for the indirect mediation pathway would need to be relatively large [36].

323

324 *Safety Monitoring*

325 Adverse events monitoring from the time informed consent is obtained until follow-up at 12  
326 weeks (using the side effect assessment scale). Laboratory parameters including total serum  
327 cholesterol, LDL, HDL, triglyceride, AST, ALT, LDH and CPK will be checked by the study  
328 physician before patient entry into the trial, and if there are any safety issues for which the  
329 patient should not be started on study medication, he/she will not be included to the study.

330

331 *Study coordination*

332 Local investigators will chair a weekly meeting with research assistants to help coordinate the  
333 study. The chief investigator will hold meetings with the research team every two weeks via  
334 Skype.

335

336 *Data protection and confidentiality*

337 For data security, consent forms and paper copies of assessment tools having any identifying  

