**Table 1: Assessment Schedule**

| Assessment                                  | Baseline | Week 2 | Week 4 | Week 8 | Week 12 | Ad hoc |
|---------------------------------------------|----------|--------|--------|--------|---------|--------|
| Medical Confirmation of Eligibility, SCID-5 | ✓        |        |        |        |         |        |
| Randomisation                               | ✓        |        |        |        |         |        |
| MADRS                                       | ✓        | ✓      | ✓      | ✓      | ✓       |        |
| HRSD-24                                     | ✓        | ✓      | ✓      | ✓      | ✓       |        |
| CGI                                         | ✓        | ✓      | ✓      | ✓      | ✓       |        |
| GAD-7                                       | ✓        | ✓      | ✓      | ✓      | ✓       |        |
| MMAS-4                                      | ✓        | ✓      | ✓      | ✓      | ✓       |        |
| Simvastatin dispensed                       | ✓        | ✓      | ✓      | ✓      | ✓       |        |
| TAU/Concomitant medication                  | ✓        | ✓      | ✓      | ✓      | ✓       |        |
| Adverse Effects Scale                       |          | ✓      | ✓      | ✓      | ✓       | ✓      |
| Basic clinical & psychiatric information    | ✓        |        |        |        |         |        |
| BMI                                         | ✓        | ✓      | ✓      | ✓      | ✓       |        |
| Biomarkers (CRP, lipids)                    | ✓        |        | ✓      |        | ✓       |        |

|                   |  |  |  |  |  |   |
|-------------------|--|--|--|--|--|---|
| Telephone contact |  |  |  |  |  | ✓ |
|-------------------|--|--|--|--|--|---|

613  
614  
615  
616  
617

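### The protocol ties adverse-event recording to a simvastatin side-effect scale, so the by-arm adverse-event summary need not reflect emergent suicidality, although suicide items are probably already rated at every visit

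*Protocol*

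**What the plan says.** - **Outcome measures** (Protocol) names the instrument: "Adverse effects will be monitored using a side effect assessment scale based on the product monograph of simvastatin".
- **Safety Monitoring** repeats it. The sentence begins "Adverse events monitoring from the time informed consent is obtained until follow-up at 12" and runs on "weeks (using the side effect assessment scale). Laboratory parameters including total serum". The laboratory checks that follow are described only as checks before entry.
- **Table 1** has a single adverse-event row, "Adverse Effects Scale", ticked at weeks 2, 4, 8 and 12 and ad hoc, but not at baseline. A separate ad hoc row provides for telephone contact.
- **Statistical Analysis** builds the harm result on these data: "To compare frequency of adverse events descriptive summaries will be presented by" treatment group, with a count model for adverse-event rates if there are enough events.
- **Exclusion Criteria** list "active suicidal ideation; pregnant or breast-feeding". The protocol does not mention suicidality by name anywhere else.
- **Screening** says that during the 12 weeks "patients will be requested to remain on a stable dose of the antidepressant they are taking". New psychotherapy is not permitted, but therapy already under way may continue.
- **Outcome measures** and **Table 1** have the MADRS and HRSD-24 rated at baseline and weeks 2, 4, 8 and 12. Both are listed as outcomes, and the MADRS total at week 12 is primary.

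**The concern.** A list drawn from a drug's monograph looks for that drug's known effects. In treatment-resistant depression, with the antidepressant dose held for 12 weeks, the foreseeable serious harms are worsening depression and suicidality. If the form follows the monograph closely and nobody asks an open question, such events have no assured route into the by-arm summary.

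That summary is the trial's harm result. A reader who finds no suicidality in it will take this as reassurance, whether or not anyone asked. The MADRS comparison does not fill the gap. It estimates a mean difference between arms, not the number of people who became newly suicidal.

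**Working it through.** **1. Which parts of the protocol name a source of adverse-event data?**

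| Section | Content | Names a further source? |
|---|---|---|
| Outcome measures; Safety Monitoring; Table 1 | the simvastatin-based scale | this is the source |
| Statistical Analysis | summary and model by arm | no |
| Randomisation and Allocation Concealment | emergency unblinding, Good Clinical Practice | no |
| Follow-up | routine psychiatric care, contactable research assistants | no |
| DSMB; TSC; Declaration of Helsinki | oversight and general standards | no |
| Methods | operating procedures will cover data definitions, collection methods and case report forms | possibly, but not shown |

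The protocol therefore fixes the instrument but not its items.

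**2. Arm sizes, from the Sample Size section.** With effect size 0.60, two-sided 5% and 90% power:

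n per arm = 2 × (1.960 + 1.282)² / 0.60² = 2 × 10.51 / 0.36 = 58.4, so 59 per arm and 118 in total.

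The stated 120 reproduces (power 0.908 with 60 per arm by the normal approximation, 0.903 by the noncentral t). Dropout: 120 / (1 − 0.20) = 150. Hence 75 randomised and 60 expected completers per arm. The point does not depend on these figures beyond the denominators.

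**3. How an empty cell would be read.** The exact one-sided 95% upper limit for zero events is 1 − 0.05^(1/n):

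- n = 75: 1 − 0.05^(1/75) = 0.0392, or 3.9%
- n = 60: 1 − 0.05^(1/60) = 0.0487, or 4.9%

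These limits hold for any zero count with these denominators, provided the event was looked for.

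**4. Illustration only.** The protocol gives no rate for emergent suicidality, so these per-participant rates over 12 weeks are assumed.

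| Assumed rate | Expected per arm (75 × rate) | Chance of at least one in 150: 1 − (1 − rate)^150 |
|---|---|---|
| 1% | 0.75 | 78% |
| 2% | 1.5 | 95% |
| 5% | 3.75 | above 99.9% |
| 10% | 7.5 | above 99.9% |

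At the lower rates the counts are so small that missing even one or two would alter the table. Nothing here says which rate applies.

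**5. Data already scheduled.** There are four post-baseline visits with both depression scales: at most 150 × 4 = 600 participant-visits, or 120 × 4 = 480 for the expected completers. If both are standard versions with a suicide item, each of these visits yields a suicidality rating. The baseline rating allows new suicidality to be told from old, which the adverse-effect scale, with no baseline rating, could not do.

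**The case against.** The strongest reply is that the form is unseen. A scale based on the monograph need not be confined to it, neither section says that nothing else will be recorded, and one free-text line would remove most of the gap. Form content also belongs in the operating procedures. This stands as a limit on the claim: a reader might infer that the adverse-event table will miss suicidality, but the protocol supports only that it need not contain it. It does not dispose of the point, because the protocol itself chose the instrument and tied monitoring to it, and an analysis plan cannot tabulate what was never asked.

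A reader might also infer that the trial collects no data on suicidality. That is not supported. With standard scales, the ratings would be in the database by arm at every visit. What is missing is their designation as safety data and a link to the harm summary.

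Nor does the protocol support reading this as an absence of serious-event reporting, or as psychiatric admissions going unrecorded. It commits that "locally and internationally accepted Good Clinical Practice will be observed". It provides for a DSMB with a safety clinician, emergency unblinding, withdrawal for adverse events, drop-out summaries by group and ad hoc telephone contact. Definitions of serious events, including admission, may properly sit in the operating procedures. None of these provisions names a further data source for the by-arm summary, but they do protect participants and may bring such events to light.

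Finally, the assumed rates show no actual shortfall. That is correct, and none is claimed.

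**Conclusion.** The point holds as a weakness in how harms are ascertained, and the change should be made. The protocol fixes one adverse-event instrument that is poorly matched to the main foreseeable harms of this population, and it does not connect suicidality ratings it probably already collects to the by-arm harm summary.

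Its size is qualitative. An empty suicidality cell could not carry the usual reading of a rate below 3.9% (75 per arm) or 4.9% (60 completers) unless the event was asked about. The conclusion rests on two assumptions that the protocol cannot settle: that the unseen form has no free-text or psychiatric item, and, for the remedy, that the MADRS and HRSD-24 are standard versions with a suicide item. No event rate is asserted, and neither the sample size nor the primary MADRS analysis is affected.

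**What to change.** 1. In Outcome measures and Safety Monitoring, state that adverse-event recording is not limited to the scale's items, and that each visit begins with an open question on adverse events before the scale is used.
2. Name the suicide items of the MADRS and HRSD-24 as a safety variable, and tabulate treatment-emergent suicidality by arm against the baseline rating. Item cut-offs and table layout can go in the analysis plan.
3. Require the rater to notify the consultant psychiatrist promptly when such an item signals new suicidality. This does not change the table, but it is the natural consequence of treating the item as safety data.
4. Leave serious-event definitions, including psychiatric admission, in the operating procedures, but state that those events enter the by-arm summary.

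The cost is form wording, one more table, coding of some unrelated complaints that an open question will bring in, and a small notification duty for raters. No new scale or visit is needed. If the existing form already has a free-text or psychiatric item, saying so in the protocol meets most of the first change.

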#### *Measurement of biomarkers*

Participants will be asked to provide two blood samples: at baseline and week 12. We aim to analyse the relationship of simvastatin to lipid and inflammatory markers and determine if this is associated with symptom change prior to a clinical effect (if detected). The biomarkers analysed will include lipid biomarkers HDL, LDL and C-Reactive Protein (CRP), a peripheral marker of inflammation.

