45 paralysis, fatigue and interpersonal sensitivity [15, 16]. Hence lipid-lowering effects of statins  
46 may also play a role in putative antidepressant effects of this class of drugs. Data from the  
47 STAR\*D trial indicate poorer treatment response to SSRIs in those with atypical depression  
48 and therefore, statins could provide genuinely novel therapeutic targets for this group of  
49 people with TRD [17].

50

51 We plan to carry out an RCT involving 150 participants with treatment-resistant depression,  
52 with the aim of determining whether the addition of simvastatin (20mg daily), a lipophilic  
53 statin that readily crosses the blood-brain barrier [18, 19], to treatment as usual (TAU) for 12  
54 weeks leads to a reduction in depressive symptoms compared with placebo added to TAU.  
55 We predict that treatment-resistant depression patients will show improvement in mood with  
56 simvastatin treatment and that the response will be associated with reduction in lipid  
57 biomarkers (i.e. plasma LDL and LDL/HDL ratio). A secondary hypothesis relates to  
58 simvastatin's effects on putative inflammatory biomarkers. High LDL and low HDL  
59 contribute substantially to immunological up-regulation in the development of  
60 atherosclerosis. Pro-inflammatory cytokine (Interleukin-6 and Tumour Necrosis Factor)  
61 levels are often altered in depressed patients and decreased by successful antidepressant  
62 therapy [20, 21]. We therefore predict that in those treatment-resistant depression patients  
63 who show improvement in mood with simvastatin treatment, that response will be associated  
64 with reduction in inflammatory biomarkers. Our mechanistic hypothesis is that the anti-  
65 inflammatory and lipid-reducing effects of simvastatin will improve neuroinflammation and  
66 thus mediate a response to simvastatin.

67   **Methods**

68   A pragmatic multi-centre, 12-week, double blind, placebo controlled randomised trial of  
69   simvastatin added to treatment as usual (TAU) for patients suffering from a DSM-5 major  
70   depressive episode that has failed to respond to at least two trials of antidepressants. This will  
71   be a parallel group study with 75 participants in each arm. Recruitment will occur at  
72   outpatient psychiatric clinics in Karachi, Lahore, Hyderabad, Rawalpindi and Quetta  
73   Pakistan. Consistency of procedures across sites will be ensured through vigorous training  

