#### 95 *Sample Size*

96 We estimate a moderate effect size of 0.60 will be reported at week 12. Assuming a type-1  
97 error of 5%, we will need to follow up 120 patients across the two groups to achieve 90%  
98 power at Week 12. With an anticipated dropout rate of 20% by Week 12, we will randomise  
99 150 participants. An effect size of 0.4 or greater for difference in MADRS scores in  
100 randomised controlled trials of antidepressants versus placebo has been suggested as  
101 necessary to suggest clinical utility for an antidepressant used as monotherapy. A sample of  
102 120 participants is therefore powered to detect moderate to large effect sizes and trends  
103 towards significance in areas of smaller effect.

104

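### The biomarker section provides for blood at baseline and week 12 only, while Table 1 and the mediation model need a week-4 sample; if the section is followed, the mediation model cannot be fitted as specified

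*Protocol*

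**What the plan says.** The protocol gives the biomarker sampling times in three places.

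- **Measurement of biomarkers:** "Participants will be asked to provide two blood samples: at baseline and week 12". This fixes both the number of samples and their times. The same section aims to relate simvastatin to lipid and inflammatory markers and to "determine if this is associated with symptom change prior to a clinical effect (if detected").
- **Table 1: Assessment Schedule:** the row beginning "Biomarkers (CRP, lipids" is ticked at baseline, week 4 and week 12, with empty cells at weeks 2 and 8.
- **Statistical Analysis:** the descriptive step looks at the association "between change in lipid/CRP (at 4 and 12 weeks) and change" in MADRS. The mediation model then jointly models the "effects of treatment on the change in lipid/CRP at 4 weeks and MADRS at 12 weeks".

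The Background gives the reason for the model: the mechanistic hypothesis is that the drug's effects on inflammation and lipids will reduce neuroinflammation and "thus mediate a response to simvastatin".

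**The concern.** The section that governs blood collection excludes a sample on which the analysis depends. It does not merely omit week 4: by giving a count and the times, it rules week 4 out. It also conflicts with its own aim. If the only post-baseline sample is taken at the visit where the primary outcome is rated, it cannot show biomarker change ahead of a clinical effect.

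At stake is the one analysis that puts the mediator before the outcome in time. The loss could not be repaired later. Once a participant has passed week 4 the sample cannot be taken, and an analysis plan cannot recover blood that was never drawn. A variable missing for everyone cannot be imputed from the trial's own data.

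**Working it through.** The point is a comparison of texts; the only arithmetic is counting.

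**Denominator.** The Sample Size section takes an effect size of 0.60, 5% type-1 error and 90% power, with 120 participants followed up. A two-sided, 1:1 t-test calculation gives 59.35 per arm, so 60 per arm and 2 × 60 = 120. With 20% dropout, 120 / (1 − 0.20) = 150. The stated figures reproduce. The point does not depend on them except for the count of 150.

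**Sampling times side by side.**

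| Source in the protocol | Baseline | Week 4 | Week 12 |
|---|---|---|---|
| Measurement of biomarkers | yes | no | yes |
| Table 1 | yes | yes | yes |
| Statistical Analysis, descriptive step | yes (for change) | yes | yes |
| Statistical Analysis, mediation model | yes (for change) | yes (mediator) | MADRS only |

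Table 1 and the Statistical Analysis section agree. The biomarker section is the outlier. The Table 1 row has all six of its cells, so a column shift in the extracted text is an unlikely explanation.

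**Size of the gap.** Two samples give at most 150 × 2 = 300 draws; three give at most 150 × 3 = 450. The difference, up to 150 draws, is the whole of the week-4 mediator.

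**Could another draw supply week 4?** Safety Monitoring lists LDL and HDL among its laboratory tests, but specifies them only before entry to the trial. No other blood draw is described.

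**What each analysis needs.**

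| Analysis | Biomarker times needed | Possible with two samples? |
|---|---|---|
| Primary MADRS comparison at week 12 | none | yes |
| Moderation by baseline lipids/CRP | baseline | yes |
| Treatment effect on week-12 biomarkers | baseline, week 12 | yes |
| Association of week-12 biomarker change with MADRS change | baseline, week 12 | yes |
| Association of week-4 biomarker change with MADRS change | baseline, week 4 | no |
| Mediation model as specified | baseline, week 4 | no |

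**Would a week-12 mediator serve instead?** Such a model could be fitted, but mediator and outcome would come from the same visit. It could not separate biomarker change that leads to improvement from improvement that leads to biomarker change.

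**The case against.** The strongest reply is that the intended design can be recovered from the document. Two of the three places agree, Table 1 is the schedule that staff would be expected to work from, and the Methods section describes central training, checklists and a manual covering data collection at every site. The affected analysis is mechanistic, and the protocol itself warns that an indirect effect would have to be fairly large to be detected at this sample size. All of this stands, and it limits how likely and how damaging the error is. It does not remove the contradiction, because the outlier is the section on blood sampling itself and nothing in the protocol says which text prevails.

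A reader might also infer more than the protocol supports:

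- **That the mechanistic hypothesis could not be examined at all.** The Background also states its predictions as associations between response and biomarker reduction. Baseline and week-12 samples can address those.
- **That consent material says two samples.** It was not available for review, so this is unknown.
- **That some sites would draw at week 4 and others would not, so that missingness follows centre.** This is possible with five recruiting cities, but it is an assumption, and the central training described makes it less likely.
- **That the analysis would fall back on a week-12 mediator.** The protocol names no fallback.
- **That a week-4 sample would settle direction.** MADRS is also rated at weeks 2 and 4, and the mediation model as described does not mention adjusting for early MADRS change. Week 4 improves the time order but does not prove causation.

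**Conclusion.** The point holds as an internal contradiction with a limited but definite consequence. If the biomarker section is followed, the mediator is missing for 150 of 150 participants, the mediation model cannot be fitted as specified, and the week-4 part of the descriptive step is lost. The 100% figure is conditional on that text being followed at every site. If Table 1 is followed everywhere, nothing is lost.

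The conclusion rests on two readings: that the Table 1 ticks were extracted in the right columns, which the Statistical Analysis wording supports, and that no undescribed draw takes place at week 4. The sample size and safety monitoring are not touched, nor are the analyses marked as possible in the table above. It should be corrected before participants reach week 4, because the loss is permanent and the repair is small.

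**What to change.** Correct the Measurement of biomarkers section to three samples (baseline, week 4 and week 12), matching Table 1 and the Statistical Analysis section. Check that the participant information and the site manual say the same, and confirm that each site is set up to draw at week 4. Follow-up visits are held by a research assistant at an agreed location, so the draw has to be planned.

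The protocol change is one sentence, and the draw is already in the schedule. The possible cost lies in the participant information: if it states two samples, it will need revision, and participants already enrolled may have to be asked again.

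If the sponsor intends only two samples, remove the week-4 tick from Table 1, take week 4 out of the descriptive step, respecify the mediation analysis with a week-12 mediator, and drop any claim that biomarker change precedes clinical change, including the aim stated in the biomarker section.
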